## Introduction

Community treatment orders (CTOs), a form of supervised community treatment (SCT), were introduced to the Mental Health Act (2007) (MHA) in England and Wales in 2008 and allow certain patients detained in hospital to continue treatment in the community following discharge under specific conditions. To be eligible for a CTO, a patient must be detained in hospital under the MHA on a section that allows for compulsory treatment. The most common inpatient treatment orders are sections 3 and 37, the former being a civil order and the latter a forensic, court-imposed equivalent for mentally ill offenders. A CTO provides the clinical team the power to recall the patient to hospital after discharge.

At CTO initiation (the point of discharge from inpatient care), there are two mandatory conditions, namely that the person subject to a CTO makes themselves available for assessment for its renewal and (where necessary) to be seen by an approved second opinion doctor (SOAD) for the purposes of assessing proposed treatment plan should the patient lack capacity in respect of their treatment. Discretionary conditions can also be specified which most often include treatment (ie, medication) adherence and engagement with services (eg, attending for appointments with professionals). CTOs do not permit compulsory (ie, forcible) treatment in the community,^1^ but those who default from these conditions may be recalled to hospital for assessment if there are grounds to suspect deterioration in their mental health and/or risk to the patient or others. Where this assessment indicates the need for further treatment, the CTO is revoked and the original treatment order applies.

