## Methods and analysis

### Data sources and study outcomes

The use of CTOs in England is recorded as part of a mandatory administrative dataset, the MHSDS, formerly known as the Mental Health Minimum Dataset, and then the Mental Health and Learning Disabilities Dataset.^23^ MHSDS collates monthly returns from health service providers on all patients in contact with secondary mental health services provided and/or funded by NHS England. This includes voluntary and involuntary inpatient treatment, outpatient attendance, day treatment and other episodes of secondary mental healthcare.

MHSDS data are based on spells of care for individual patients. Since 2011, the dates on which specific care spells start and end have been included. Care spell dates can therefore be used to determine duration of CTO use and hospital (re)admissions. Four years of MHSDS data will be used covering the period 2011/2012 to 2014/2015, hereafter referred to as the study period. MHSDS records contain a unique patient identifier code which will be used to link patient care spells across the study period. This identifier will also be used to link patient records to the Office for National Statistics (ONS) Mortality Database, to ascertain patient deaths. Access to and linkage of, these different administrative data sets will be facilitated by the ESRC Administrative Data Research Network.

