Next, to examine associations between CTO use and a range of outcomes, a cohort of patients will be constructed consisting of a treatment group (those who have been on a CTO) and a matched control group (those who are eligible but who have not been on a CTO). To prevent bias arising from secular changes in clinical practice, we will frequency match these groups according to the start date of the CTO (CTO group) and the end date of the CTO-eligible section of the MHA (non-CTO group), with tolerance limits determined after inspection of the data. As these dates are the point within the study period at which patients in both treatment groups are discharged from hospital, they represent the index date for each arm of the study. Models based on the cohort of matched patients will be used to test associations between SCT use and patient outcomes: total time spent in hospital, time to first readmission and mortality. For total time spent in hospital, count models based on Poisson or negative binomial distributions will be estimated. For time to first readmission, discrete-time survival analysis models will be estimated. For mortality, binary response models based on the logistic distribution will be estimated. To control for confounding by indication, we will adjust analyses for the propensity of being placed on SCT,^33^ with propensity scores being modelled using the pool of available variables which will include age, sex, ethnicity, diagnosis and previous admissions (where known). CCMMs based on this cohort will be used to test for the overall ‘average’ effect of CTO on each of the study outcomes. The models will also assess whether there is significant spatial and temporal variation around these average effects and estimate the extent to which this is associated with patient, local area and health service characteristics, including the length of time that patients are on CTOs.

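### Length of time on a CTO is used to explain variation in the CTO effect, but it accrues after the index date and is cut short by death and by revocation, so its association with the outcomes is biased

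*Protocol article*

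**What the plan says.** The Data analysis section of the protocol article sets up a matched cohort and models three outcomes in it: "total time spent in hospital, time to first readmission and mortality". Follow-up starts at discharge. For the CTO group that is the CTO start date and for controls the end of the eligible section; of these dates the article says "they represent the index date for each arm of the study".

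After the average effect, the models are to estimate how far variation around it is associated with patient, area and service "characteristics, including the length of time that patients are on CTOs".

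The model types are stated. Hospital time gets a Poisson or negative binomial count model. For the others: "For time to first readmission, discrete-time survival analysis models will be estimated" and "For mortality, binary response models based on the logistic distribution will be estimated".

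The Introduction describes how a CTO can end after recall to hospital: "Where this assessment indicates the need for further treatment, the CTO is revoked and the original treatment order applies". The section on data sources says that one set of records supplies both quantities: "Care spell dates can therefore be used to determine duration of CTO use and hospital (re)admissions".

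**The concern.** Age, diagnosis or area deprivation are known at the index date. The length of a CTO is not: all of it accrues during the time in which hospital days, readmission and death are being counted, and those events help to determine it. A patient who dies three months after discharge cannot have a two-year CTO. A patient recalled and revoked at four months has a short CTO because of the readmission. Days detained after revocation are also no longer CTO days, so the primary outcome and the covariate compete for the same observation window.

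No stated safeguard covers this. The propensity score models being placed on a CTO, not how long it lasts. Matching is on the index date. The stated limitations are confounding by indication, residual confounding, bias and missing data.

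The result at stake is a statement that longer CTOs go with fewer deaths, readmissions or bed days. The article promises findings of direct policy relevance, and such a statement could be read as support for longer compulsion when the definition of the covariate produced it.

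**Working it through.** The article gives no figure to reproduce, so the check asks what association appears when CTO length has no effect at all. **All rates below are assumptions.**

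**1. Readmission, CTOs of at least 6 months against shorter ones**

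Assumptions: planned CTO length C is exponential with mean 1.5 years; first readmission T is exponential with hazard h per year, independent of C; follow-up is 2 years; a share p of readmissions revoke the CTO. Deaths are ignored here.

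Write a = P(C > 0.5) = exp(−0.5/1.5) = 0.7165, s = exp(−0.5h), g = 1 − exp(−1.5h) and E = 1 − exp(−2h).

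- All patients: events E, person-years E/h.
- Long CTO: events a[p·s·g + (1−p)E]; person-years a[p·s(0.5 + g/h) + (1−p)E/h].
- Short CTO: the remainder.

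With h = 0.5: s = 0.7788, g = 0.5276, E = 0.6321, E/h = 1.2642.

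- p = 1. Long: 0.2944/0.8679 = 0.339 per year. Short: 0.3377/0.3963 = 0.852. Ratio 0.40.
- p = 0.5. Long: 0.3737/0.8869 = 0.421. Short: 0.2584/0.3774 = 0.685. Ratio 0.62 (0.615).
- p = 0.25. Long: 0.4133/0.8964 = 0.461. Short: 0.2188/0.3679 = 0.595. Ratio 0.78 (0.775).
- p = 0. Both 0.5. Ratio 1.00.

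| Share revoked | h = 0.3 | h = 0.5 | h = 0.8 |
|---|---|---|---|
| 100% | 0.42 | 0.40 | 0.37 |
| 50% | 0.63 | 0.62 | 0.60 |
| 25% | 0.79 | 0.78 | 0.76 |
| 0% | 1.00 | 1.00 | 1.00 |

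The true ratio is 1.0 in every cell.

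**2. The planned model types, per extra year on a CTO**

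Simulation under no effect. Assumptions: follow-up uniform from 0.25 to 4 years; readmission 0.2, 0.4 or 0.7 per year; death 0.02 per year; CTO ended by other routes at 0.5 per year. Realised duration was a fixed covariate in a quarterly discrete-time logistic model, a logistic model for death, and a negative binomial model for bed days with a follow-up offset.

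| Share revoked | Readmission OR | Bed-day rate ratio | Death OR |
|---|---|---|---|
| 100% | 0.29–0.46 | 0.50–0.54 | 0.56–0.62 |
| 50% | 0.71–0.74 | 0.81–0.83 | 0.54–0.58 |
| 25% | 0.87 | 0.90–0.93 | 0.54–0.56 |
| 0% | 1.01 | 0.94–1.04 | 0.52 |

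The death result hardly depends on revocation, because death always ends the CTO.

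**3. Early CTO discharge of well patients**

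Same simulation at 0.4 readmissions per year, with patient frailty (SD 0.8 on the log hazard) and low-risk patients leaving their CTO sooner. With full revocation the readmission OR stays below 1 (0.39–0.64). With 25–50% revocation and strong selective discharge it is 0.99–1.32, and the bed-day ratio is 0.93–1.11. The death OR stays at 0.56–0.65 throughout.

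**4. Landmark at 6 months**

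Under the assumptions of step 2, patients still at risk at 6 months were split by CTO status on that day and only later events were counted. The on/off rate ratios were 1.00–1.01 for readmission and 0.98–0.99 for death. This run had no frailty, so it shows that the immortal time is removed, not that selection is.

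**The case against.** The strongest objection is that the article never says total, realised or fixed duration. A discrete-time model can take a time-updated term, and coding is commonly left to a fuller document that is not shown. That is fair for readmission. It does not help for hospital time or death: as described, each has one outcome per patient, so realised duration is the natural reading there. Naming duration as an explanatory characteristic is the article's own choice.

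A reader might infer three stronger claims, none of which the document supports:

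- *Every readmission ends the CTO.* The Introduction says that revocation follows recall and an assessment showing a need for further treatment. It does not say that all readmissions, for example voluntary ones, have this effect, and no revoked share is given.
- *Longer CTOs are bound to look protective on every outcome.* This is firm for mortality. For readmission and bed days it is the likely direction, but step 3 shows that it can vanish or reverse.
- *The study's main result is compromised.* The average CTO versus non-CTO contrast does not use duration.

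The magnitudes also rest on assumed rates, and the crude ratio in step 1 is not itself a planned model. Step 2 answers the second of these by using the planned model types. The first stands.

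**Conclusion.** The point holds for the duration part of the effect-variation analysis (aim 3) and no further. Realised CTO length is partly set by the outcomes that it is meant to explain. With no true effect and the assumed rates, the death OR per extra CTO year is about 0.5 to 0.65 in every scenario tried. For readmission, the rate ratio for CTOs of at least 6 months against shorter ones runs from about 0.4 (all readmissions revoke) through 0.6 (half) and 0.8 (a quarter) to 1.0 (none). Bed days behave similarly. Selective early discharge can push the readmission and bed-day associations to 1 or above, and an association whose sign depends on unknown discharge practice cannot be interpreted either.

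**What to change.** Do not enter realised total CTO duration as a fixed covariate in any outcome model.

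- **Readmission (discrete-time model):** use CTO status, or cumulative CTO time, as it stands at the start of each interval. This does not carry over to the other two models.
- **Hospital time and mortality:** use a landmark, for example 6 months after index, with 12 months as a sensitivity analysis. Among patients alive and out of hospital on that day, compare those still on a CTO with those whose CTO has ended. Count only later outcomes and adjust for baseline covariates.

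The change is one of analysis-plan wording, and the person-period data are already needed for the readmission model. The price is precision, because events before the landmark are not counted. With hazard h, the share of 2-year first readmissions that falls before a landmark at L years is [1 − exp(−Lh)]/[1 − exp(−2h)]. For h = 0.3 to 0.8 this is 31–41% at 6 months and 57–69% at 12 months, so the 12-month loss is substantial.

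Selection into longer CTOs remains. Patients revoked and discharged again before the landmark fall in the group whose CTO has ended, and well patients may leave theirs early. This should be reported as a limitation.

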Finally, we will use outputs from our CCMMs to populate predictive models of healthcare resource use incorporating the predicted impact of CTOs. We will model differences in treatments costs (eg, bed days and number of contacts with mental health staff) between patients who are and are not on CTOs. We will also quantify the administrative burden of CTOs, using protocols for mandated governance processes (eg, Mental Health Act Review Tribunals and SOADs) that apply to the use of CTOs. Projected costs associated with different plausible future trajectories of CTO use will be calculated and a probabilistic sensitivity analysis will be presented for each projection based on estimates of parameter uncertainty derived from the CCMMs.

CCMMs will be estimated in MLwIN using Markov chain Monte-Carlo (MCMC) Bayesian methods.^34^ This approach is suited to the complexity of the MHSDS and will provide unbiased measures of variation in CTO use and outcome, and associations with patient, local area and health setting characteristics. MCMC modelling diagnostics, together with measures of multilevel variation, will be used to evaluate different models to quantify where, and for whom, associations and variation occurs.^35–37^

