## Ethics and dissemination

To ensure patient confidentiality and to meet data governance requirements, analyses will be carried out in a secure microdata laboratory at the ONS using de-identified data. Reporting of the study will be consistent with the Strengthening the Reporting of Observational Studies in Epidemiology guidelines.^38^

CTOs are used more often than originally anticipated in England. Although many clinicians continue to see their value,^39^ uncertainty and concern about their use has been expressed by regulators and legislators.^3 40^ Both have called for the sort of nuanced evidence about the benefits and hazards of CTO use in real-world settings which can only come from large-scale, population-based, observational research. The purposes of this study are to describe the practice in respect of CTO use and duration, to estimate associations with, and spatial variation in, outcomes, and to understand where, and for whom, CTOs might be of benefit. We will also model the economic costs and benefits of current patterns of CTO use.

This will be the largest and most complete study of its kind in England. The national scope and representativeness of the study sample, deriving from routine clinical activity, is a major strength, as is the duration of follow-up. Study limitations are those that affect observational and secondary research, particularly confounding by indication, residual confounding and bias. Issues of data quality (including missing data) are important sources of the latter.^41^ The study findings will be of direct policy relevance, and we plan to share them directly with those bodies working in this area at the earliest opportunity.

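### The cost projections carry model parameter uncertainty but not the residual confounding of the CTO effect that the article itself expects, so their intervals may be materially too narrow and off-centre

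*Protocol article*

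**What the plan says.** All of this is in the protocol article; no separate analysis plan is shown.

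- **Source of the CTO effect in the cost model** (Methods and analysis, Data analysis, third stage): "we will use outputs from our CCMMs to populate predictive models of healthcare resource use incorporating the predicted impact of CTOs".
- **Scenarios** (same place): "Projected costs associated with different plausible future trajectories of CTO use will be calculated".
- **Uncertainty** (same place): "a probabilistic sensitivity analysis will be presented for each projection based on estimates of parameter uncertainty derived from the CCMMs".
- **A cost component from outside the models** (same place): "We will also quantify the administrative burden of CTOs, using protocols for mandated governance processes".
- **Control of confounding** (Data analysis, second stage): "To control for confounding by indication, we will adjust analyses for the propensity of being placed on SCT". The variables named for the score are age, sex, ethnicity, diagnosis and, where recorded, earlier admissions. The list is open-ended.
- **Limitations** (Ethics and dissemination): those of observational research, "particularly confounding by indication, residual confounding and bias". The strengths and limitations box after the abstract lists confounding by indication together with bias from missing data.

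**The concern.** A posterior distribution from a propensity-adjusted multilevel model expresses sampling error and variation between areas and providers. It does not express error from a confounder that is not in the model. The article expects such error, and the indication makes it plausible. The Introduction says CTOs were brought in for repeated admissions linked to non-adherence. Both plausibly drive time in hospital, yet adherence is not among the variables named for the propensity score.

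The other layer of the projections does not fill the gap, because trajectories of future CTO use change how many people are on CTOs and leave the effect per person unchanged. Aim 2 in the Introduction speaks of associations; by the third stage these have become an impact that generates costs, with no stated bridge.

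At stake is what can be concluded from the fourth aim, on financial costs and benefits. The abstract reports that randomised studies found few positive impacts while observational designs were more favourable. Parameter uncertainty within one observational model cannot express that kind of disagreement. A narrow cost interval could therefore be read as firm evidence of a saving or a cost that residual confounding might remove.

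**Working it through.** The article states no sample size, effect size, unit cost or interval width, so there is no figure to reproduce. What follows is an illustration on the bed-day rate ratio, to see whether the omission could matter.

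**Anchors in the article.** Almost five thousand CTOs were issued in 2016–2017 (orders, not patients, and after the study period); about 30% of eligible patients are placed on one; the data cover four years.

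**Assumed, not in the article.**
- CTO patients: n1 = 5,000 to 20,000 (the upper end is 4 × 5,000).
- Controls: n0 = n1, or n0 = n1 × 0.7/0.3 from the 30% share.
- Negative binomial dispersion: k = 1 to 6 (variance = mean + k × mean²).
- Between-provider standard deviation of the effect: τ = 0 to 0.3, over T = 60 providers.
- One unmeasured binary confounder that multiplies bed days by g, with prevalence p1 in CTO patients and p0 in controls.

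**Step 1: standard error of the log rate ratio.** SE = √[k(1/n1 + 1/n0) + τ²/T]. The Poisson term 1/mean is left out because it is small against k for stays counted in days.
- Smallest (n1 = 20,000, n0 = 46,667, k = 1, τ = 0): √(0.0000500 + 0.0000214) = 0.0085. The 95% limits lie a factor of 1.017 either side of the estimate.
- Middle (n1 = n0 = 10,000, k = 3, τ = 0.1): √(0.000600 + 0.000167) = 0.0277; factor 1.056.
- Largest (n1 = n0 = 5,000, k = 6, τ = 0.3): √(0.0024 + 0.0015) = 0.0624; factor 1.130.

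**Step 2: bias.** B = [1 + p1(g − 1)] / [1 + p0(g − 1)], b = log B.

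**Step 3: coverage of the nominal 95% interval.** Φ(1.96 − b/SE) − Φ(−1.96 − b/SE). For example, with the moderate confounder and the middle SE, b/SE = 0.0426/0.0277 = 1.54, so coverage is Φ(0.42) − Φ(−3.50) = 0.66.

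| Confounder | g; p1 vs p0 | B | b | Coverage, SE 0.0085 | SE 0.0277 | SE 0.0624 |
|---|---|---|---|---|---|---|
| Weak | 1.2; 35% vs 30% | 1.07/1.06 = 1.009 | 0.009 | 80% | 94% | 95% |
| Moderate | 1.5; 40% vs 30% | 1.20/1.15 = 1.043 | 0.043 | 0.1% | 66% | 90% |
| Strong | 2; 50% vs 30% | 1.50/1.30 = 1.154 | 0.143 | 0% | 0.1% | 37% |

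**Step 4: width if the bias is carried as an extra standard deviation.** Multiplier = √(SE² + b²)/SE. Over the grid this is 1.01 to 1.49 (weak), 1.2 to 5.1 (moderate) and 2.5 to 17 (strong).

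Two readings follow. The shortfall runs from negligible to severe, depending on inputs the article does not give. Also, B moves the centre of the interval, so widening alone does not repair it. The direction is assumed here (confounder commoner in CTO patients, ratio pushed up); coverage would be the same for an equal shift the other way.

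**The case against.** The strongest defence is that a probabilistic sensitivity analysis conventionally covers parameter uncertainty. The article says its analysis is based on this, not that it is limited to it. It plans propensity adjustment, admits residual confounding openly, and may leave a bias analysis to a fuller document. This is fair as far as it goes, and the mere absence of a bias analysis from a condensed article would not be a finding. What remains is a stated choice: the article fixes the basis of the intervals and takes the CTO effect from the same models, while expecting an error that neither covers.

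Four stronger readings are tempting and are not supported.

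- *That the intervals will be far too narrow.* Every input to the size is assumed, and the weak-confounder row is close to nominal. A bed-day ratio interval is also not a cost interval: staff contacts and administrative burden enter too, and no unit costs are given.
- *That the models carry sampling error only.* The second stage assesses spatial and temporal variation around the average CTO effect, so the posteriors include variation between units. That is why τ is in the formula above.
- *That the article contradicts itself by promising that its estimation "will provide unbiased measures of variation in CTO use and outcome".* That sentence concerns measures of variation and associations with patient, area and setting characteristics. It does not name the CTO effect on outcomes and is at most loose wording.
- *That confounding is declared the main weakness.* It is listed alongside missing data and data quality, without a ranking.

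The trial evidence also needs care: the article reports no significant benefit in three randomised trials but criticises their size, participation and crossover. It shows that designs disagree, not which design is right.

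**Conclusion.** The point holds in a limited form. As described, each projection's probabilistic interval reflects model parameter uncertainty, the trajectories vary uptake alone, and acknowledged residual confounding of the CTO effect enters neither. Because a national dataset is likely to make parameter uncertainty small, the intervals may be materially too narrow and off-centre. The article does not allow the amount to be computed. The illustrative coverage range, from about 95% down to about 0%, rests wholly on the assumed cohort sizes, dispersion, provider variation and confounder values. It shows that the omission can matter, not that it does.

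**What to change.** In the third stage of Data analysis, add to each projection:

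1. **A scenario with no CTO effect on bed days**: the rate ratio is set to 1 and the administrative burden kept, so the reader sees the projected cost if the association is not causal.
2. **The strength of unmeasured confounding at which the projected saving or cost difference becomes zero.** This should be worked out on the cost scale. Because CTOs carry an administrative cost, a bed-day saving is cancelled before the rate ratio reaches 1. With other costs equal, net saving per person = c·D·(1 − R) − A, for bed-day cost c, control bed days D, true ratio R and administrative cost A. Break-even is at R = 1 − A/(cD), below 1 whenever A is positive.
3. **A label on the probabilistic intervals**: conditional on no unmeasured confounding of the CTO effect.

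A bias distribution on the CTO rate ratio is optional. If one is used, its centre and range need justification, and it should allow a directional shift: a distribution centred on no bias widens the interval but leaves its centre where it was.

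The cost is a little more simulation work and projections that look less certain. No new data are needed.
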